#### Exclusion criteria

If the patients meet any of the following criteria at the screening visit, they will not be eligible for the study:

Primary exclusion criteria involve (1) pregnancy or lactation, (2) inability to comprehend or engage in the task, (3) acute cardiovascular or pulmonary ailments, or (4) acute non-cardiopulmonary disorders susceptible to or exacerbated by exercise performance (e.g., infection, renal failure).

### Who will take informed consent? {26a}

Patients slated for elective major surgery will undergo eligibility screening conducted by the study team within outpatient departments. Furthermore, all physicians will receive training and orientation regarding the recruitment process to enhance recruitment efficacy. Eligible patients will be informed about the study by trained study physicians or principal investigators delegated by the participating center. Written informed consent will be obtained by a trained investigator prior to any study-specific procedures.

### Additional consent provisions for collection and use of participant data and biological specimens {26b}

Furthermore, given the incomplete understanding of the molecular mechanisms and effects of prehabilitation, patients will be asked to consent to tissue research (using resection specimens). This research aims to elucidate mechanisms of vascular repair, microenvironmental changes, and mitochondrial health. These endeavors are considered ancillary projects necessitating supplementary funding. At present, consent will solely be sought for participation in these ancillary projects, in addition to the regular informed consent for the clinical trial.

## Interventions

### Explanation for the choice of comparators {6b}

The comparator used is the digitized informational app (Ready4Op). Ready4Op version 1 is a classic digital textbook without any interventional approaches to the patient. There is a basic demographic survey of height, weight, BMI, diet preferences, and fitness level of each patient before prompted to the content area which triggers individualization of the content. The content consists of 9 categories of which the 6 freely available consist of the prehab-specific content. In more than 50 subchapters, the patients receive valuable evidence-based information about the perioperative phase and can use the digital textbook as a knowledge base. There is no exchange or storage of data on a server, the demographics remain on the individual smartphone. There will be no direct readout. To better understand what the patients gained from the application, a set of standard PROMs will be documented to compare the results to the interventional group described above. The choice of comparator is the minimum recommended information patients should receive before major surgery. Experience and data show that this information often comes much too short and therefore is more than standard in an average preoperative preparation. The resource-sparing information on perioperative options to improve the individual situation before major surgeries is standard of care and does not deviate from common practice.

### Intervention description {11a}

#### Prehab App

The Prehab App is a medical software designed to create individually tailored aerobic interval exercise training programs for patients aged 18 years and older requiring major elective surgery. It will be a medical device class IIa and is currently developed by Capreolos GmbH, a spin-off company of the Goethe University Frankfurt/Main. The app encompasses a structured risk assessment (Fig. 2), based on demographic data and individual risk factors. The patient will then be stratified into a specific risk group utilizing the Karvonen method [17]. A blood sampling takes place.

**Fig. 2 Fig2:**
[figure not shown]
Schematic layout of the app surface with exemplary risk scoring

The physician assesses the patient’s risk group using a desktop computer or the app. Then, the standalone software generates a personalized risk-based endurance exercise program and calculates the target heart rate (HR), incorporating maximum heart rate, resting pulse, and individual risk factors. Afterwards, the personalized training program is installed on the patients’ smartphones, where they will start with a 3–6-week aerobic interval training regimen (Fig. 1).

Prior to exercising, patients receive structured guidance as per the instruction manual and are screened for contraindications such as acute respiratory infections.

Before each session, patients complete a baseline QLQC-30 survey and a 6-min walking test. Each interval session lasts 47 min, including 5 min of warm-up and 5 min of cool-down, and will be performed 3 to 4 times. The training consists of alternating 2-min intense and 3-min less intense intervals. Heart rate and distance will be monitored during both the initial and final 6-min walking tests, as well as during individual training sessions. This monitoring will be facilitated via an Application Programming Interface (API) that interfaces with a smartwatch worn on either the right or left wrist tracking heart rate and distance.

Patients follow instructions on their wearable to stay within their threshold levels displayed on the screen, indicated by green (within) or red (outside) coloration. Vibration alerts signal training outside defined thresholds. Following the 6-MWT or exercise, patients are directed to a summary page to review data, and patient-reported outcome measures (PROMs) regarding symptoms experienced during exercise are collected. The Prehab program ends with a final 6-MWT and QLQC-30 survey. Then a second assessment calculating the risk scoring again by a physician follows directly before surgery. A second blood sampling takes place. The intervention results are then correlated with the 90-day follow-up data. The 90-day follow-up is undertaken as a telephone interview.

For the patient, no other equipment than a smartphone having The Prehab App installed and a smartwatch is needed. The app works with all common smartwatch and smartphone software on the market (e.g., iOS, Android).

The software facilitates home-based, remote exercise sessions, which can occur outdoors in nature or indoors on a treadmill, indoor cycle, or indoor track, at any time of day. Patients have autonomy in selecting their exercise environment, including factors such as lighting, noise level, terrain, location, and timing, to suit their schedule and preferences.

The comparator group is using the Ready4Op App which gives information generally provided preoperatively.

After completing the Prehab program via the app as described above, upon return to the hospital and prior to surgery, a second risk assessment is conducted. Here, delta values are calculated, indicating improvements, a stable condition, or a decline in assessed points, serving as decision support for continuing with the operation or assigning alternative therapies.

Throughout the program, a safety check is initiated on both the physician and patient displays according to an algorithm derived from the software’s risk management. To track app or device failure, safety, and misuse scenarios, testing the app’s alarm settings will be conducted at the same time. A 24/7 emergency hotline connects patients to the treating hospital. Physicians can monitor the exercise data of each patient in their department to track progress, while individual patients can review their progress within the app.

#### Assessments during the treatment phase

Intervention visits are performed weekly during the prehabilitation period and contain the evaluation of PROMs, compliance, safety audit, and retrieval of digitized data (V2–V7) (Table 1). Blood samples will be collected before the first and after the last interval training to further evaluate the safety of app-based exercise training. Additionally, the validity of the Karvonen method, including risk adjustments based on defined risk factors, will be assessed and correlated with the occurrence of clinical symptoms. To do so, 1–3 days before surgery, reassessment is conducted by performing a 6-min walking test and by evaluating patient history, risk factors, anemia, and heart rate (V5/V8).

**Table 1 Tab1:**
[figure not shown]
Treatment and visit week scheme. Schedule of enrolment, interventions and assessments of the LUMOS trial

#### Assessments during the follow-up phase

After surgery before discharge, patient status and operative procedure as well as ICD codes and postoperative complications are collected (V6/V9). Ninety days after surgery, patient status as well as Dindo–Clavien scores are evaluated. After surgery, patients will undergo follow-up assessments on days 7 and 90 to evaluate the occurrence of any (serious) adverse events or device failures.

One year after surgery, the patient’s status will be evaluated again. The end of the trial is defined as the last 1-year follow-up of the last patient.

### Criteria for discontinuing or modifying allocated interventions {11b}

Patients can leave the study at any time for any reason if they wish to do so without any consequences.

In case too much data is missing (e.g., missing baseline or all of the follow-up patient-reported outcome measures (PROMs), study visits), the patient will be replaced by a new patient. Early termination or temporary suspension may be recommended exclusively by the DSMB or sponsor following DSMB recommendation in case of unexpected serious safety concerns, unacceptable adverse event patterns, major protocol violations compromising participant safety, or regulatory authority requests such as ethics committee or the BfArM.

Termination criteria: unexpected safety concerns such as a significant increase in frequency or severity of serious adverse events related to the intervention, an unacceptable benefit-risk ratio therefore indication of potential risks of the intervention outweighing its anticipated benefits, a regulatory or ethical requirement due to regulatory, ethical or legal concerns, major protocol violations or GCP violations that compromise participant safety, data integrity or scientific validity, insufficient recruitment or feasibility despite corrective measurements, rendering completion of the study within the planned timeframe scientifically or operationally unfeasible, poor intervention adherence that prevents meaningful evaluation of the primary endpoint despite corrective actions, data integrity concerns, funding or logistical concerns preventing continuation of the study.

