### Outcomes {12}

#### Descriptive measures, survival analyses, and cost analyses

Primary outcome: occurrence of any postoperative complication within 90 days after surgery according to the Clavien–Dindo classification (grades I–V).

Secondary outcomes: 1-year overall survival, 6-min walking distance, QLQ-C30 quality of life score, adherence and compliance, device failures, length of stay, days on ICU/IMC, readmission rates, hospital costs.

There will be an intention to treat analysis of all included patients fulfilling the in- and exclusion criteria. Data will undergo descriptive evaluation and assessment for normal distribution utilizing the Kolmogorov–Smirnov test with Lilliefors correction. Results will be presented as median or mean with standard deviation and interquartile ranges, and/or odds ratios with 95% confidence intervals, where applicable. Survival data will be computed as the time interval from the date of surgery to the date of death, or until censoring if patients are alive at their last visit/contact.

An intention-to-treat analysis will encompass all enrolled patients meeting the predetermined inclusion and exclusion criteria. Additionally, a per-protocol analysis will be conducted.

Compliance analysis in the intervention group includes the analysis of the number of exercises performed and the exercising within the predefined thresholds. We do expect a total of 191 6-MWTs delivering 65,000 pulse points and approximately 53 Mio. pulse points from 191 patients performing 10 exercises of 47 min each during the program that will define compliance as outlined in the following. Compliance of patients in the intervention group will be categorized according to the app algorithm (green: >75% of exercises performed and >75% of all measured values are green or yellow, yellow: 50–75% of exercises performed and 50–75% of all measured values are green or yellow, red: <50% of exercises performed and <50% of all measured values are green or yellow). Comparative compliance in the control group and the intervention group will be based on a descriptive comparison of the weekly safety calls in each group during the interventional phase as PROM analysis.

Surgical procedures and indications will be categorized based on OPS and ICD-10 codes. Subgroup analyses will be conducted using chi-square testing, *T*-testing, Kaplan–Meier survival analysis, and multivariate regression analysis.

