### Sample size {14}

#### Sample size and power calculation

Based on findings from the literature and our pilot trial “Protego Maxima,” we observed an approximate complication rate or morbidity, as per the Dindo–Clavien classification, of 60% up to 90 days post-surgery [18]. Evidence from randomized-controlled trials suggests a relative reduction in morbidity due to prehabilitation ranging from 30 to 50% [19–21]. Hence, we estimated a clinically meaningful and feasible reduction to a complication rate (Clavien–Dindo I–V) of 45% at day 90 post-surgery in the intervention arm compared to the control arm. Potential center-related heterogeneity may influence the observed effect size. This will be addressed analytically by adjusting for center effects in the statistical models.

Given a study power of 80%, significance set at *p* < 0.05, and an anticipated dropout rate of 10%, we calculated a required sample size of 173 patients per treatment arm. We accounted for a dropout rate of 10% in our calculations. Utilizing the chi-square test and probability calculations in two groups led to a sample size of 191 patients per treatment arm (382 patients in total, including dropouts), in accordance with methods described by Rosner [22].

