## Statistical methods

### Statistical methods for primary and secondary outcomes {20a}

Data will be analyzed using IBM SPSS (version 29 or more current version, if applicable). Surgical procedures and indications will be categorized based on OPS and ICD-10 codes. Subgroup analyses will be conducted using chi-square testing, *T*-testing, Kaplan–Meier survival analysis, and multivariate regression analysis. The center will be included as a stratification variable. Data will be descriptively evaluated and tested for normal distribution with the Kolmogorov–Smirnov test with Lilliefors correction. Data will be expressed as median or means with standard deviation and interquartile and/or odds ratios with 95% confidence intervals where appropriate. Survival data will be calculated as time intervals from the date of their death to the date of operation, respectively be censored, if they are alive at their last visit/contact. Subgroup analyses will be conducted for predefined categories including cancer versus non-cancer surgery, abdominal versus non-abdominal procedures, and higher-risk versus lower-risk patients. Surgical category will additionally be included as a covariate in multivariable analyses to account for potential heterogeneity in baseline risk. The primary analysis will follow the intention-to-treat principle. Multivariable regression models will be used to assess treatment effects while adjusting for study center and relevant baseline characteristics. Where appropriate, mixed-effects regression models including study center as a random effect will be applied to account for the multicenter study design.

Costs will be derived from data recorded in the electronic case report form (eCRF). Costs for a day on ICU are 1500€/day, for a day on the IMC 1000€, and on general ward 500€. The DRG generated by each case will be subtracted from the sum on each treatment unit and the final sums compared between the arms. This is a two-sided approach using *T*-testing of two independent groups and a *p *value < 0.05 is regarded clinically significant.

The 95% confidence interval of the fixed effect size will be used to assess whether the treatment difference reaches the minimally clinically important difference.

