### Methods in analysis to handle protocol non-adherence and any statistical methods to handle missing data {20c}

The primary outcome will be assessed using an intention-to-treat analysis. Missing data will be reduced to a minimum by using the appropriate measures described above. Patients whose data are missing will be treated in accordance with the intention to treat principle. As the app does not allow to proceed when critical data is missing, the probability of this event is very low.

In general, it is strictly forbidden to not adhere to the clinical trial protocol outlined in the protocol. Deviations from the original statistical analysis plan can be recommendations from the DSMB or the regulatory authorities. Potential reasons can be justifiable in case patients need to be protected from potential harm in emergency situations. These situations will be documented and immediately reported to the independent review board and to the competent authority in analogy with the SAE reporting procedures. In addition, a risk-benefit evaluation will be made for those events and for the whole study cohort based on DSMB recommendations. Based on the conclusion, an amendment will be prepared, the study will be carried on, or the study will be stopped. Preventing actions include a dedicated and structured onboarding for all investigators involved. This will be documented on trial logs and stored in the ISF and TMF. Study procedures will be supported by clear checklists and supporting material for the investigators.

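### The rule that replaces patients with too much missing data reaches randomised patients and, read as ordinary replacement, conflicts with the intention-to-treat primary analysis; the app-based missing-data rationale does not cover the 90-day endpoint

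*Protocol article*

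**What the plan says.** Section {11b} sets a replacement rule. It applies when too much of a patient's data is missing, and its examples are no baseline data or none of the follow-up patient-reported "outcome measures (PROMs), study visits), the patient will be replaced by a new patient". No threshold is given.

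Three places commit to intention to treat:
- Outcomes {12}: "An intention-to-treat analysis will encompass all enrolled patients meeting the predetermined inclusion and exclusion criteria".
- Statistical methods {20a}: "The primary analysis will follow the intention-to-treat principle".
- Missing data {20c}: "The primary outcome will be assessed using an intention-to-treat analysis". It adds that patients with missing data are handled on the same principle.

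The sample size section {14} gives 173 per arm, raised to 191, and says: "We accounted for a dropout rate of 10% in our calculations".

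On the likelihood of missing data, {20c} says: "As the app does not allow to proceed when critical data is missing, the probability of this event is very low". The primary endpoint is any Clavien–Dindo grade I–V complication within 90 days of surgery. Complications are recorded before discharge and again at day 90 (follow-up assessments under {11a}). The intervention description adds: "The 90-day follow-up is undertaken as a telephone interview".

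**The concern.** Randomisation takes place at or just after the baseline assessment ({16a}, {16b}). Missing baseline data might therefore be found before allocation, but missing follow-up PROMs or visits cannot be. To that extent the rule selects patients on what happens after randomisation.

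The trial is open label. One arm does repeated 47-minute interval sessions with a smartwatch, and the other reads an information app. Stopping contact could plausibly depend on health, burden and arm. Because the trigger has no threshold, staff who know the allocation would judge when it is met. As worded, a patient whose Clavien–Dindo outcome is known from hospital records could still be replaced for having no follow-up PROMs.

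At stake is who belongs to the primary comparison. Two analysts could build different primary data sets from this text, and one of those sets would no longer be the randomised one.

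**Working it through.** **1. The plan's own sample size.** Inputs from {14}: 60% versus 45%, power 80%, significance level 0.05. The two-sided test is taken from {20b}, since {14} does not restate it.

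n per arm = [z(0.975)·√(2·p̄·q̄) + z(0.80)·√(p1·q1 + p2·q2)]² / (p1 − p2)², with p̄ = 0.525 and q̄ = 0.475.

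= [1.960·√0.49875 + 0.842·√0.4875]² / 0.15² = (1.384 + 0.588)² / 0.0225 ≈ 172.8, so 173. This matches.

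173 × 1.10 = 190.3, so 191. This matches too. Dividing by 0.90 instead gives 193, a small difference.

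**2. Is replacement needed for power?** With 191 randomised per arm and 10% without an outcome, 191 × 0.90 = 171.9, about 172 observed. Power at 172 is Φ[(0.15·√172 − 1.384)/0.698] = Φ(0.835) = 79.8%, against a target of 80%. If replacement restored 191 complete patients per arm, power would be 83.8%. The rule thus provides for dropout a second time.

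**3. What replacement could do to the comparison.** The replacement rates and the risks among replaced patients are assumptions; the document gives neither. Take no true effect, 60% risk in both arms, and replaced patients removed from the analysis. If a fraction f with risk r is removed, the rate among those retained is (0.60 − f·r)/(1 − f).

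Example: f = 0.10 and r = 0.90 give (0.60 − 0.09)/0.90 = 56.7%. With f = 0.05 the result is (0.60 − 0.045)/0.95 = 58.4%.

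Spurious difference in favour of the app, in percentage points:

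| Replaced, intervention vs control | r = 50% | r = 60% | r = 70% | r = 80% | r = 90% |
|---|---|---|---|---|---|
| 10% vs 0% | −1.1 | 0 | 1.1 | 2.2 | 3.3 |
| 10% vs 5% | −0.6 | 0 | 0.6 | 1.2 | 1.8 |
| 15% vs 5% | −1.2 | 0 | 1.2 | 2.5 | 3.7 |
| 10% vs 10% | 0 | 0 | 0 | 0 | 0 |

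The probability of a false finding in favour of the app is Φ[(d − 1.96·SE0)/SE1], with 191 analysed per arm, SE0 pooled and SE1 unpooled. For 10% versus 0% at r = 90%, d = 0.0333 and both standard errors are about 0.0504, which gives Φ(−1.30) = 9.7%. At r = 70% and 80% it is 4.1% and 6.4%. The nominal value is 2.5%. For 10% versus 5%, the two-sided type I error at r = 70%, 80% and 90% is 5.2%, 5.6% and 6.4%, against a nominal 5%. For 15% versus 5% it is 5.7%, 7.8% and 11.3%.

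**4. Does the app rationale reach the endpoint?** Complications are documented at the hospital before discharge and assessed again at day 90. The only route named for day 90 is a telephone interview, and clinical data are held in the eCRF ({18a}). An entry block in an app used before surgery cannot prevent loss at that stage. In the control arm, Ready4Op stores nothing on a server and has no readout ({6b}). The protocol itself plans for 10% dropout ({14}) and lists loss to follow-up above 15% as a foreseeable threat ({11b}).

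**The case against.** The strongest reply is that {11b} does not define an analysis set. The sections that do are consistent with one another, so replacement may mean only recruiting an extra patient while the original stays in the analysis. On that reading the contradiction disappears. The text does not exclude it, but does not say it either, and ordinary usage points the other way. A reader might infer that replaced patients are certain to be dropped and that the analysed set is completers only. The document does not establish that.

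A second reply is that the trigger is narrow. The PROM example is the absence of all follow-up PROMs, and the qualifier may extend to the visits as well. This stands: a patient who misses some questionnaires or a visit is not clearly caught. If all visits are also missing, there may be no 90-day outcome to lose. Replacing a patient whose outcome is known is therefore a possibility under the wording, not a stated intention.

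Third, a reader might infer that the rule favours the app. Nothing shows that missingness differs by arm or that replaced patients are at higher risk. Weekly safety calls and PROMs are planned in both arms. The larger figures above rest on one-sided assumptions.

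Fourth, {20c} also relies on other measures: completeness checks and queries in the eCRF, retrieval from health records ({18a}) and contacting patients to complete follow-up ({18b}). These apply to both arms and are relevant. They leave the app sentence as a poor reason, though not the only safeguard.

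**Conclusion.** The point holds in a limited form. The replacement rule reaches randomised patients and does not say whether they remain in the analysis. Read as ordinary replacement, it is incompatible with the intention-to-treat statements in {12}, {20a} and {20c}. It can bias the primary comparison, but it cannot be said that it will, or in which direction. Under the assumptions shown, with replaced patients at 70% to 90% risk, the spurious benefit is 1.1 to 3.3 points for 10% replaced in the intervention arm only, and 0.6 to 1.8 points for 10% versus 5%. With equal rates and risks it is zero, and with lower-risk replaced patients it reverses. For scale, the target difference is 15 points.

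The rule duplicates an allowance already made: without it, the expected power is 79.8%. Separately, the app-based reason for expecting little missing data does not apply to the 90-day endpoint in either arm.

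**What to change.** - In {11b}, delete the replacement sentence or limit it to patients not yet randomised.
- State that every randomised patient is kept in the primary analysis in the arm assigned, and that 382 is the number randomised.
- State that the 90-day Clavien–Dindo outcome is sought regardless of app use or PROM completion, unless consent is withdrawn.
- In {20c}, replace the app sentence with a rationale and a missing-outcome method that cover the 90-day endpoint in both arms. Multiple imputation with a sensitivity analysis would be one choice; the details belong in the statistical analysis plan.

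Cost: no extra patients. Recruitment began in December 2025, so this is an amendment during recruitment and, if judged substantial, needs the approvals described in {25}. Some incomplete records will stay in the analysis, and the possible gain from 79.8% to 83.8% power through replacement is given up. It is best settled before any patient is replaced.
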